**Fig. 1 f0005:**
[figure not shown]
Example of information module on the option of saying no to sexual acts.

**Fig. 2 f0010:**
[figure not shown]
Example of exercise module on the different steps for desensitisation exercises.

Technical support is provided by an internet support team when participants report technical problems to an eCoach. A dedicated Gmail account is added for communication with participants should technical problems with the platform arise.

### Collection of data

2.6

Online assessments are conducted at baseline (T0), posttreatment (6 weeks after randomisation, T1), and at follow-up (9 months after randomisation, T2). Self-reported online questionnaires generally have the same psychometric properties as paper-and-pencil administrated questionnaires (Buchanan, 2003). Three emails are sent as reminders for each assessment. A flowchart of the study is presented in Fig. 3. Among the first 15 participants, the drop-out rate between baseline and post-treatment is 33%, while 47% of those participating in post-treatment are lost to follow-up.

**Fig. 3 f0015:**
[figure not shown]
Flowchart of the study.

Medical records will be assessed after proper authorization by the clinic, in accordance to the ethical application, to control for parallel clinical treatment during the intervention period.

### Sample size calculation

2.7

Sample size calculation was based previous clinical experience based on self-reported vulvar pain using a Visual analogue scale, which is a Likert scale between 0 and 10, where 0 represents no pain and 10 represents the worst possible pain; this is regularly assessed with questions on pain at intercourse or tampon insertion, which are posed during the first appointment with gynaecologists at Uppsala University Hospital. A minimum of 26 patients in each group at each time point is estimated to give 80% power for ascertain a difference between the groups at a significance level of *p* < 0.05 for a minimum clinically significant improvement of at least 1.2 units in the Visual analogue scale for vulvar pain, as described above, with an estimated 20% drop-out rate.

### Study outcomes

2.8

#### Primary outcomes

2.8.1

Pain intensity at vaginal intercourse and tampon test is assessed using an 11-point Likert numeric rating scale (Foster et al., 2009; Wammen Rathenborg et al., 2019). Self-reported pain is rated between 0 (”no pain”) and 10 (”worst possible pain”). The tampon test has a fair to moderate week-to-week test-retest reliability and is significantly associated with pain at intercourse and pain intensity (Foster et al., 2009).

Impact of pain on sexual function is assessed by asking “How do you rate your pain today?” and is rated from 0 to 3, where 0 corresponds to never having pain at vaginal intercourse and 3 corresponds to severe pain that often/always prevents intercourse.

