**Methods:**

We will randomise 52 patients to either guided internet-based intervention with CBT with (ACT) components or no intervention during the waiting period for treatment as usual. Online assessments are conducted at baseline, posttreatment, and at follow-up after 9 months. The primary outcome measure is provoked vulvar pain. Secondary outcomes are depression, anxiety, sexual function, and quality of life. Linear-mixed effect models will be used to assess the effect of the internet-based intervention on vulvar pain, pain acceptance, depression, anxiety, sexual function, and quality of life over time, by applying the intention-to-treat approach. Continuous data will be analysed with general linear models using intention-to-treat and also per protocol approaches to assess the effects of the intervention at different time points. Ordinal and binary data will be analysed with Mann Whitney's test, Fischer's exact test and multivariate logistic regression, respectively.

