### Statistical analysis plan

2.9

Linear mixed effect models will be used to assess the effect of the internet-based treatment on vulvar pain, pain acceptance, depression, anxiety, sexual function, and quality of life over time, by applying the intention-to-treat approach. Variables that vary significantly between groups at baseline will further be adjusted for in the model. Linear mixed modelling is a frequently recommended method for its abilities to handle missing data and correlated observations in repeated-measures data (Gueorguieva and Krystal, 2004; Yoo, 2010). The best-fitted model to the data consists of an unstructured covariance matrix using the restricted maximum likelihood (REML) estimation procedure. Baseline, posttreatment and follow-up measures will be used as repeated measures and intervention/control group will be used as fixed factors.

As significant drop-out is common in internet-based interventions, further analyses will be performed. Continuous data will be analysed with general linear models using besides intention-to-treat also per protocol approaches to assess the effects of the intervention on vulvar pain, depression, anxiety, sexual function, and quality of life at different time points (post-treatment and follow-up). Last observation carried forward (LOCF) will be used for the intention-to-treat analysis. Complementary analysis using worst case imputation and analysis using a per-protocol approach without imputation will also be carried out. Effect size will be calculated with Cohen's d. *P* values less than 0.05 will be considered statistically significant. Ordinal (impact of pain on sexual function) and binary data (willingness to perform tampon test and attempt at vaginal intercourse) will be analysed with Mann Whitney's test, Fischer's exact test and multivariate logistic regression, respectively, to assess differences between groups at posttreatment and follow-up. The binary data are referring to secondary outcomes and will be analysed using a per protocol approach only. Descriptive statistics at baseline and the corresponding changes during follow-up both will be provided in tables and graphically. All analyses will be completed using the IBM SPSS statistical package.

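### Three unranked primary outcomes are assessed at two time points against an unadjusted 0.05, and no outcome, time point or contrast is designated as primary

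*Protocol article*

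**What the plan says.** The abstract of the protocol article (Methods) is in the singular: "The primary outcome measure is provoked vulvar pain". Section 2.8.1, whose heading is plural, gives more than one. It opens with "Pain intensity at vaginal intercourse and tampon test is assessed using an 11-point Likert numeric rating scale", which is two scores, each 0 to 10. It then adds a third, ordinal from 0 to 3: "Impact of pain on sexual function is assessed by asking". The three are not ranked.

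Section 2.7 does not settle the matter. It powers the trial for one difference of 1.2 units on a 0-10 pain scale and describes that pain as arising at intercourse or at tampon insertion, without choosing between them. It asks for 26 women per group at each time point.

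Section 2.9 starts with "Linear mixed effect models will be used to assess the effect of the internet-based treatment on vulvar pain" and a list of other outcomes, over time and by intention to treat. It then introduces further analyses because of drop-out: "Continuous data will be analysed with general linear models using besides intention-to-treat also per protocol approaches", with effects assessed "at different time points (post-treatment and follow-up". The intention-to-treat version of these uses LOCF, and worst-case imputation and an unimputed per-protocol analysis are described as complementary. The 0-3 item gets a Mann-Whitney test "to assess differences between groups at posttreatment and follow-up". One threshold covers everything: P "values less than 0.05 will be considered statistically significant".

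**The concern.** A 0.05 threshold holds the trial-level error at 5% only if one test decides the trial, or if a rule links several tests. This article has three outcomes with primary status, two assessments after baseline and no linking rule. A report that followed it faithfully could present as the main result whichever pain score and time point crossed 0.05.

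The opposite reading, that all must be significant, would control the error. But the sample size was set for one difference, so its 80% would then not be the trial's chance of success. The article chooses neither reading, and the two lead to different conclusions from the same data.

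**Working it through.** **The plan's own figure.** Section 2.7 gives 26 per group, 80% power, p < 0.05, a difference of 1.2 and 20% drop-out. It gives no SD, so the figure can only be solved backwards. With SD = 1.2 / [(1.960 + 0.842) × √(2/26)], the implied SD is 1.2 / 0.777 = 1.54 if all 26 are evaluable. If 20% are lost, 26 × 0.8 = 20.8 remain and the implied SD is 1.38. Either way the calculation covers one comparison. The article states no familywise error rate.

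**Counting the tests.**
- Three outcomes (section 2.8.1) × two time points (section 2.9) = 6.
- The two 0-10 scores tested once each in the mixed model, plus the 0-3 item at both time points: 2 + 2 = 4.
- One test per outcome = 3.

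**Assumptions not in the article.** Success means at least one p < 0.05, tests are two-sided, and a range of correlations is tried. The article gives no correlation; section 2.8.1 says only that tampon-test pain is associated with intercourse pain.

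**Independent tests.** Familywise error = 1 − (1 − 0.05)^k.
- k = 6: 1 − 0.95^6 = 1 − 0.7351 = 0.265
- k = 4: 1 − 0.95^4 = 1 − 0.8145 = 0.185
- k = 3: 1 − 0.95^3 = 1 − 0.8574 = 0.143

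**Correlated tests.** Each statistic is √ρ × (shared normal) + √(1 − ρ) × (own normal). The share of 2,000,000 draws with any absolute value above 1.960 is the error rate. The first row below is the exact formula.

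| Assumed ρ | 6 tests | 4 tests | 3 tests |
|---|---|---|---|
| 0 | 26.5% | 18.5% | 14.3% |
| 0.3 | 24.2% | 17.4% | 13.6% |
| 0.5 | 20.7% | 15.6% | 12.6% |
| 0.7 | 16.4% | 13.0% | 10.9% |
| 0.8 | 13.9% | 11.4% | 9.8% |
| 0.9 | 10.9% | 9.4% | 8.4% |

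Letting the correlation differ between outcomes (0.3 to 0.8) and between time points (0.3 to 0.7), with the product of the two across both, gives 16.0% to 24.6% for six tests (500,000 draws each).

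**If all had to succeed.** Suppose each of the two 0-10 scores has the stated 80% power at one time point. Joint power is 0.8 × 0.8 = 0.64 if they are independent and at most 0.80 if they are perfectly correlated. Adding T2 or the 0-3 item cannot raise it.

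**If all six were kept with a Bonferroni correction.** The per-test level is 0.05 / 6 = 0.0083, with critical value 2.638. At 26 per group and SD 1.54, power is Φ(2.802 − 2.638) = about 56%. Restoring 80% needs 2 × (2.638 + 0.842)² × (1.544 / 1.2)² = 40.1, so 41 per group.

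**The case against.** Four objections deserve an answer.

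- **The analysis method is largely settled.** Section 2.9 puts the intention-to-treat mixed model first and calls the others further or complementary. The Discussion presents per protocol as a complement to intention to treat, and worst-case imputation as a guard against a known weakness of LOCF. A reader might infer that the trial may pick freely among four analyses of each pain score. The wording does not support that, and the four variants do not apply to the ordinal item. This objection stands. The gap is in outcome, time point and contrast.

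- **The error rate is not a property of the trial.** A reader might infer that the false-positive rate is 16% to 26%. That range is correct arithmetic for six tests at correlations from 0.7 down to 0, but the article fixes neither the correlations, nor the count of six, nor an any-one-significant rule. Independence is also unlikely for related pain scores repeated in the same women. This stands too: the figures are conditional, and 16% is not a floor.

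- **A condensed article may leave test ordering to a separate plan.** That is fair for detail. It does not explain why the abstract has one primary measure and section 2.8.1 has three, or why section 2.9 states a single unqualified threshold. Those are things the article says.

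- **The 0-3 item's wording is a distraction.** Its stem asks about today, while its anchors describe how often pain occurs at or prevents intercourse. The study is run in Swedish and the English may be a translation. The wording has no bearing on the error rate and is not relied on here.

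**Conclusion.** The point holds as a failure to designate. Three scores carry primary status against one in the abstract, two time points are assessed, and 0.05 applies to each without adjustment. Following the stated rule therefore does not hold the trial-level error at 5%.

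The size depends on assumptions. Under an any-one-significant rule, six tests give up to about 26% (independent), about 21% at correlation 0.5, 16% at 0.7 and 11% at 0.9. One test per outcome gives about 10% to 14% for correlations from 0.8 down to 0. Every scenario computed is above 5%. Under an all-must-succeed rule the error is controlled, but the 80% power does not carry over. The documents support neither a single figure for the error rate nor a claim that the method of analysis is left open.

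**What to change.** Before the data are analysed, record the following as decided without sight of results. The date and the blinded status matter because recruitment began in 2016 (section 2.3).

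1. Name one primary pain score and one time point. T1 fits the aim, which concerns the waiting period before clinical treatment.
2. Name the test: the group contrast at that time point from the intention-to-treat mixed model, two-sided 0.05.
3. Test the remaining primary scores and T2 in a fixed order, or move them to secondary, and make section 2.8.1 agree with the abstract.
4. State outright that the LOCF, worst-case and per-protocol analyses are sensitivity analyses.
5. If tampon-test pain is chosen, state how women unwilling to perform the test are handled. Section 2.8.2 treats unwillingness as an outcome of its own, so missing scores may be related to treatment.

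The cost is a documented amendment and fewer outcomes that can carry a confirmatory claim. No additional patients are needed, whereas keeping all six tests under Bonferroni would cut power to about 56% at the planned size.

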#### Secondary outcomes

2.8.2

Secondary outcomes include pain acceptance, depression, anxiety, sexual function, and quality of life. To better our primary outcome measures, two other variables will also be analysed: unwillingness to perform the tampon test and abstinence from vaginal intercourse, both measured as binary variables.

Chronic pain acceptance questionnaire (CPAQ) is a self-assessment form used for patients with chronic pain and measures pain acceptance (Feliu-Soler et al., 2018; McCracken et al., 2004; Reneman et al., 2010). CPAQ is divided into two subscales: activity engagement (participation in activities despite living with pain) and pain willingness (attempts to avoid and control pain as pain management (ineffective coping) (Feliu-Soler et al., 2018; McCracken et al., 2004; Wicksell et al., 2009). The form consists of 20 statements that can be rated between “never true” to “always true”. CPAQ has good internal consistency and similar psychometric properties both when administered online or via paper-and-pencil (Fish et al., 2010; Wicksell et al., 2009).

The Female Sexual Function Index (FSFI) is an instrument for measuring female sexual function and consists of 19 questions within 6 domains: sexual desire, arousal, lubrication, orgasm, satisfaction, and pain (Rosen et al., 2000; Wiegel et al., 2005). Questions are rated on a Likert scale from 0 or 1 to 5, where 0 corresponds to no attempt at intercourse. Higher FSFI scores indicate better sexual functioning (Ter Kuile et al., 2006). Test-retest reliability has appropriate level of stability, while the internal consistency of the instrument and its subscales are satisfactory to good (Ter Kuile et al., 2006). The ability of the scale to predict the presence or absence of sexual complaints is considered excellent (Ter Kuile et al., 2006).

The Female Sexual Distress Scale-Revised (FSDS-R) is an instrument for measuring female sexual distress and consists of 13 questions (Derogatis et al., 2008). The score varies between 0 and 48 and each question can be rated from 0 (never) to 4 (always) (Derogatis et al., 2008). Higher FSDS-R scores indicate more sexual distress (Ter Kuile et al., 2006). The instrument has excellent reliability and good discriminant validity (Derogatis et al., 2008; Ghassami et al., 2014).

The Beck Anxiety Inventory (BAI) is a scale that measures anxiety using a list of 21 anxiety symptoms and has high reliability and good validity (Beck et al., 1988; Muntingh et al., 2011). The score varies between 0 and 63 and symptoms are rated from 0 (“not at all”) to 3 (“severely, I could barely stand it”) (Muntingh et al., 2011).

The Montgomery-Åsberg Depression Rating Scale (MADRS-S) is a 9-item scale for measuring depressive symptoms and has satisfactory internal consistency (Fantino and Moore, 2009). The score varies from 0 to 54 and symptoms are rated between 0 and 6 (Hollandare et al., 2010). Higher scores indicate more depressive symptoms. A high correlation has been found between administration of the survey via the internet and using paper and pencil assessments (Hollandare et al., 2010).

The Revised Dyadic Adjustment Scale (rDAS) is an instrument for measuring dyadic adjustment in relationships. It has acceptable levels of construct validity and adequate internal consistency (Busby et al., 1995; Crane et al., 2000). The score ranges from 0 to 69, where a score of 48 is the cut-off point between distressed and non-distressed couples (Crane et al., 2000).

The Satisfaction with Life Scale (SWLS) is a 5-item scale for measuring life satisfaction. Each item is scored from 1 to 7 and the possible range of total scores varies from 5 (low satisfaction) to 35 (high satisfaction). A score of 20 represents a neutral point in the scale and higher scores indicate greater satisfaction with life (Diener et al., 1985; Pavot and Diener, 2008). The scale has good reliability and acceptable validity (Hultell and Petter Gustavsson, 2008; Maroufizadeh et al., 2016).

The EQ-5D (EuroQol-5-dimension questionnaire) is an instrument for measuring quality of life and consists of two parts: one part with 5 questions about different dimensions of health-related quality of life, and one part with a Visual Analogue Scale where the respondent assess their overall health status (Aubry et al., 2017; Janssen et al., 2013). The instrument has good construct validity and excellent responsiveness to change (Aubry et al., 2017).

Other collected data are sociodemographic information, exposure to violence, and social support. The ENRICHD Social Support Instrument (ESSI) is a 7-item self-reported instrument for measuring perceived social support (Vaglio et al., 2004). A 5-item Likert scale ranging from “none of the time” to “all the time” is used (Lett et al., 2009). Higher scores indicate high social support (Vaglio Jr et al., 2004). The instrument has high reliability and acceptable validity (Vaglio Jr et al., 2004). The number of visits related to vulvodynia will be retrieved from participant's medical records.

All measures will be collected at T0, T1, and T2, except rDAS (collected only at T0 and T2). Sociodemographic information and answers to questions about exposure to violence, general pain, and comorbidities are collected at T0.

Patients receive a small value gift certificate when they have filled out T1 and another one when they have filled out T2.

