The treatment consisted of six different modules, spanning a 6-week treatment period, based on an ACT manual for the treatment of patients with chronic pain (Buhrman et al., 2013), and adapted for patients with vulvodynia by a multidisciplinary team (gynaecologist, psychologist physiotherapist and midwife) with experience in treating patients with vulvodynia. The treatment was CBT-based, with ACT components, with a multidiscplinary approach; the CBT/ACT components were used as a framework during the entire treatment, for example, the modules 3 and 4 had information and exercises about valued direction and management of negative thoughts (Table 1). The modules are divided into information and treatment assignments (Figs. 1 and 2). The information modules contain knowledge about anatomy, pelvic floor muscle function, sexuality, chronic pain, and vulvodynia. Some parts of patient education are also given in video format, such as information regarding pelvic floor anatomy instruction, pelvic floor exercises is given by a physiotherapist, and information about vulvodynia, communication with partner, and sexuality is given by a midwife. The exercise modules contain exercises related to CBT-based ACT. Further, daily exercises were recommended and consisted of mindfulness, pelvic floor muscle exercises, and desensitisation exercises. The participants in the control group, on request, are given access to the internet-based treatment after 10.5 months from study inclusion. The average number of words per module is 7401 (module 1: 8143, module 2: 8760, module 3: 7638, module 4: 6755, module 5: 8813, and module 6: 4294). It is estimated that about 30 min per day are needed to complete one module per week. Written feedback, consisting of positive reinforcement related to a participant's assignment, is provided weekly to the participants on their submitted assignments after module completion by the eCoaches.

**Table 1 t0005:** Description of the six different modules included in the intervention group.

Module	Information	Exercises	Daily training
1. Introduction	Vulvodynia Chronic pain Primary and secondary suffering CBT, ACT and internet-based treatment	Primary and secondary pain Circle of pain Expectations and planning Personal commitments	Mindfulness exercise
2. Pelvic floor	Anatomy of the vulva Pelvic floor Stress and anxiety Exposure	Things I have done Willingness diary	Mindfulness exercise Pelvic floor exercise Exposure exercise

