3. Values	Valued direction Willingness	What do you want your life to stand for? Life compass Why willingness? To have hope	Mindfulness exercise Pelvic floor exercise Exposure exercise
4. Thoughts	Negative thoughts Alternative attitude Sexuality	To have and to be a thought The little word”and” Reformulate goals	Mindfulness exercise Pelvic floor exercise Exposure exercise
5. Relations	Relations Sexual identity Desire Communication Exposure	Body contact Stoplight	Mindfulness exercise Pelvic floor exercise Exposure exercise
6. Maintenance	Summary of the sections The new contract Maintenance Closure	Reflections Evaluate my commitments Maintenance plan	Mindfulness exercise Pelvic floor exercise Exposure exercise

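### The plan gives non-attempt no stated place in the 0–10 pain scores, although attempting plausibly depends on pain and on treatment arm

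*Protocol article*

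**What the plan says.** Section 2.8.1 of the protocol article lists the scores: "Pain intensity at vaginal intercourse and tampon test is assessed using an 11-point Likert numeric rating scale". It states neither a recall window nor a rule for a woman who did not perform the act. The same section lists a 0–3 item on the impact of pain, where "3 corresponds to severe pain that often/always prevents intercourse". Section 2.8.2 places non-attempt among the secondary outcomes: "two other variables will also be analysed: unwillingness to perform the tampon test and abstinence from vaginal intercourse, both measured as binary variables".

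Section 2.5 describes content that bears on attempting: "daily exercises were recommended and consisted of mindfulness, pelvic floor muscle exercises, and desensitisation exercises". Table 1 adds exposure exercises from module 2 onwards, a willingness diary in module 2, and in module 3 an exercise headed "Why willingness? To have hope". The caption of Fig. 1 points the other way: "Example of information module on the option of saying no to sexual acts".

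Section 2.9 analyses pain with an intention-to-treat linear mixed model, giving as a reason that "Linear mixed modelling is a frequently recommended method for its abilities to handle missing data and correlated observations in repeated-measures data". It then adds general linear models with LOCF, worst-case imputation and a per-protocol analysis without imputation, and introduces them by reference to drop-out. The 0–3 item goes to a Mann–Whitney test. The two binary non-attempt variables are restricted to a per-protocol analysis.

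**The concern.** A woman can stay in the trial, complete every questionnaire and still have no 0–10 pain score because she did not attempt. This differs from drop-out in two ways. It plausibly depends on how severe the pain would have been, and the intervention is built to change it. Attempting is therefore a post-randomisation variable that may differ between arms.

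If treatment brings more women with severe pain to attempt, mean observed pain in that arm rises and a true benefit looks smaller. If it leads more women to decline, mean observed pain falls with no change in pain. A mixed model under missing at random corrects only for what the woman's observed scores predict. LOCF replaces the gap with a score from an earlier visit. A woman who never attempts gives neither method a score to use.

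The two variables that would reveal a shift in attempting are analysed per protocol only. A reader of the results could not tell from all randomised women whether a pain difference reflects pain or a change in who attempts.

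**Working it through.** **Planning figure.** Section 2.7 gives 26 per group, 80% power, a difference of 1.2 and p < 0.05 (two-sided assumed). It gives no SD, so 26 cannot be reproduced directly. Solving n = 2(1.96 + 0.84)²·SD²/1.2² for SD gives 1.54 if 26 is the evaluable number, and 1.38 if 26 already includes 20% drop-out (26 × 0.8 = 20.8 evaluable). There is no separate allowance for non-attempt. With SD 1.54 and 26 women present per group, power is 71% if 80% have a score (20.8) and 58% if 60% do (15.6), before any bias.

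**Illustration 1.** None of these inputs comes from the documents, apart from the effect of 1.2 and the back-solved SD. Pain has mean 7 and SD 1.54, with correlation 0.5 between T0 and T1. At T0, 70% attempt. The propensity to attempt is correlated 0.5 with lower pain. There are 400,000 women per arm. Entries are intervention minus control at T1. *Baseline-adjusted* uses women with both scores and stands in for the mixed model. *Worst case* sets non-attempters to 10.

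| True effect | Attempt, control / intervention | Observed only | Baseline-adjusted | LOCF | Worst case |
|---|---|---|---|---|---|
| 0 | 60% / 60% | 0.00 | 0.00 | 0.00 | 0.00 |
| 0 | 60% / 80% | +0.22 | +0.17 | +0.14 | −0.53 |
| 0 | 50% / 80% | +0.35 | +0.27 | +0.19 | −0.81 |
| 0 | 70% / 50% | −0.23 | −0.17 | −0.11 | +0.56 |
| −1.2 | 60% / 60% | −1.20 | −1.20 | −0.83 | −0.71 |
| −1.2 | 60% / 80% | −0.97 | −1.03 | −0.89 | −1.48 |
| −1.2 | 50% / 80% | −0.86 | −0.94 | −0.84 | −1.76 |
| −1.2 | 70% / 50% | −1.44 | −1.38 | −0.84 | −0.04 |

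I re-ran this and it agreed within about 0.02. Varying the attempt–pain correlation from 0.3 to 0.7 in the second row gives +0.14 to +0.32 (observed only), +0.10 to +0.24 (adjusted), +0.08 to +0.20 (LOCF) and −0.56 to −0.48 (worst case). The adjusted figures are 0.10/1.2 = 8% to 0.24/1.2 = 20% of the target difference.

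Three things follow. With equal attempt rates the observed and adjusted analyses recover the truth. With unequal rates all methods move away from zero under no effect. In those rows worst case has the opposite sign to the other three, so the planned analyses can contradict each other.

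**Illustration 2.** Control pain has mean 6.5 and SD 1.5. The attempt probability is 1/(1 + exp(2·(pain − 7 − shift))), with shift applied to the intervention arm only.

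- A true benefit of 1.2 appears as 0.77 among attempters with shift 0, and 0.55 with shift +1. The implied attempt rates are 61% in control against 84% or 94%.
- Adjusting for a fully observed baseline score (correlation 0.5) improves this to about 0.85 and 0.69, but does not restore 1.2.
- With no pain effect and a shift of +1 or −1, the adjusted arms differ by +0.31 or −0.40 (intervention minus control). The adjusted test rejects in 13% to 15% of trials at 26 per arm.
- A rank test with non-attempters placed worst has about 73% and 86% power in the two benefit cases. It also rejects in 10% (shift +1) and 20% (shift −1) of trials with no pain effect.

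**The case against.** The defence has substance. A reader might infer that the primary comparison is simply one between self-selected subsets of attempters. The documents do not support that, for four reasons:

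- That non-attempters have no score is inferred from the outcome definition. The questionnaire is not shown.
- The mixed model is intention-to-treat with baseline as a repeated measure, so a woman with a score at any visit stays in. The subset description is exact only for observed-case analyses.
- Worst-case imputation is planned. If it covered non-attempt it would come close to a worst-rank analysis: setting non-attempters to 10 gave 70% and 91% power in the benefit cases of illustration 2. What remains is that Section 2.9 motivates it by drop-out and does not extend it to non-attempt.
- Pain that prevents intercourse is already the worst category of the 0–3 primary item, which is analysed by ranks and can be answered without attempting.

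A reader might also see a conflict with the Female Sexual Function Index, where "0 corresponds to no attempt at intercourse". Section 2.8.2 reports this as the scoring of the instrument, not as an analysis decision, so it is not a contradiction in the plan.

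The magnitudes are open to challenge too. They rest on assumed attempt rates, and the largest come from an attempters-only comparison that is not the planned main analysis. The evidence that content could lower attempting is one figure caption, and it has no bearing on the tampon test.

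None of this supplies a rule for non-attempt in the 0–10 scores, or an analysis of attempting in all randomised women.

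**Conclusion.** The point holds in a limited form. For the two 0–10 scores, the article plans methods that assume missing at random or carry scores forward, while one expected source of gaps plausibly depends on pain and on arm. The pain comparison could be biased in either direction. The documents give no attempt rates, no SD and no recall window, so the size cannot be estimated. The illustrations show only that baseline adjustment reduces the bias without removing it, and that the planned analyses can disagree in sign. The conclusion rests on two assumptions: that non-attempters have no score, and that the exposure and willingness content changes attempting. The 0–3 primary item is not affected. The change is worth making, but the point does not show that the mixed-model result would be invalid.

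**What to change.** Keep the mixed model as planned and prespecify the following before analysis.

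1. For each 0–10 score, add a supplementary analysis in all randomised women with questionnaire data at T1 and T2, with non-attempters ranked worst. Alternatively, state that the planned worst-case imputation applies to non-attempt, reported separately from drop-out.
2. Analyse unwillingness and abstinence in all randomised women, not per protocol only.
3. Show attempt rates by arm beside each pain result, and interpret a pain difference in their light. Do not require both tests to be significant: in the benefit cases of illustration 2, joint power was only 42% and 25%.
4. Section 2.8.2 records non-attempt as binary and mentions no reasons. If reasons for abstaining were not collected, use a score of 3 on the 0–3 item to identify pain-related abstinence from intercourse, or show the analysis with and without all abstainers ranked worst.

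The cost is one extra analysis per pain score and a wider analysis set for two variables already collected. The downside is that the composite mixes pain intensity with willingness to attempt and responds to willingness alone (10% and 20% rejection with no pain effect in illustration 2). It should therefore support the mixed model and not replace it.
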